### Statistical analysis

#### Analysis of health system gaps

Analysis of data from the retrospective chart review of patients will quantify clinical and process impediments in VL testing system; results will inform the VL testing pathway, a QIP and required augmentation of TIER.Net. Proportions of patients with outcomes of interest will be tabulated; 95% confidence intervals will be calculated using clustered standard errors to take correlation within clinic into account. Factors associated with true missing viral load (not documented in TIER.Net or present in the patient chart) will be analysed using logistic regression with robust standard errors.

#### Evaluation of the trial intervention

The effect of the intervention on the primary outcome (proportion of patients with VL suppression) will be estimated using a two-stage approach based on cluster (i.e. clinic)-level summaries [19]. The cluster-level approach, although less statistically efficient than methods based on individual level regression, is more robust when there are a relatively small number of clusters. Briefly, in the first stage, the proportion with VL suppression in each clinic will be calculated, and logarithmically transformed. In the second stage, the cluster-level summaries will be compared using a stratified t-test to test the null hypothesis of no intervention effect. Since equal numbers of clinics will be allocated to the 2 arms within each stratum, the unadjusted risk ratio (RR) for the intervention effect will be calculated as the ratio of geometric mean proportion with VL suppression for the 5 clusters in each arm. The 95% confidence interval (CI) will be calculated with the variance estimated from the residual mean square in a two-way analysis of variance of the log proportions on stratum and trial arm, incorporating a stratum by trial arm interaction. An adjusted analysis based on cluster-level summaries may also be done to account for covariate imbalance at baseline, using a similar two-stage process. All covariates will be pre-specified in a detailed analysis plan. In the first stage, an individual-level logistic regression will be done, including terms for stratum and all covariates except the intervention effect, and ignoring clustering. After fitting the regression model, a residual for each cluster will be calculated as the ratio of the observed to the predicted number of events. If the intervention has no effect, the residuals of the two arms should be similar on average. In contrast, if the intervention has an effect, we expect the residuals to differ systematically. Therefore, in the second stage, we will compare the residuals between the trial arms using the methods described above; residuals will be log transformed for the analysis. Analysis of the intervention effect on the secondary outcomes will be done using the same approach. A detailed statistical analysis plan will be prepared before to data analysis.

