#### Evaluation of the intervention

We estimate that during the 3 month recruitment phase, an average of 150 patients who have been on ART for ≥ 12 months will attend each clinic. Based on our previous work, we expect that around 50% of patients in the control arm will have a VL measurement and be virally suppressed at the end of follow-up. With 5 clinics per arm, assuming a coefficient of variation, k, of 0.20, and a sample size of 150 patients per clinic, we would have 80% power to detect an increase in the proportion of patients who have a VL measurement and are virally suppressed from 50% in the control arm to 77% in the intervention arm (Table 1).

**Table 1 Tab1:** Numbers needed to demonstrate an improvement in viral load monitoring, for different assumptions regarding clinic size and effect sizes

Number of clinics per arm	Number of patients per clinic^1^	Coefficient of variation (k)	% with VL suppressed in control	% with VL suppressed in intervention	Power (%)
5	100	0.20	45	67	71
5	100	0.20	45	70	80
5	100	0.20	50	74	71
5	100	0.20	50	77	80
5	100	0.20	55	80	70
5	100	0.20	55	84	80
5	150	0.20	45	66	70
5	150	0.20	45	69	80
5	150	0.20	50	73	70
5	150	0.20	50	77	80
5	150	0.20	55	80	70
5	150	0.20	55	84	80

^1^Harmonic mean to account for varying facility size

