### Allocation and blinding

The 10 clinics will be randomly allocated to the intervention (5 clinics) and control (5 clinics) arms. Randomisation will be stratified on clinic size, defined by the number of HIV-related visits per month (2 strata). Restricted randomisation will be used to ensure balance between study arms on the following important covariates: proportion of HIV patients who are male; proportion of HIV patients who are aged < 25 years. A computer programme will be used to prepare a list of all permissible randomised combinations; community leaders will be invited to make a random selection from the list at a public ceremony. The randomisation list will be prepared by an independent AHRI statistician and will be concealed until after randomisation. It will not be possible to blind the research staff and nurses to the intervention.

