#### Evaluation of the intervention impact

TIER.Net has information on HIV-positive individuals on ART including unique South African Identification number, age, sex, date of ART initiation, viral load results and dates, CD4 count results and dates, type of ART regimen, status of the individual (whether still in care, lost to follow up or dead), and dates of clinic appointments. The clinical charts of the 150 participants per clinic who are in the evaluation cohort will be reviewed to extract these baseline data for entry into REDCap. These will be repeated after each participant has completed 12 months of follow up in their clinic/cluster to capture documentation of VL being measured, test data and the results of the VL. These data will be used to evaluate the impact of the intervention on VLM and virological suppression, and on the treatment failure cascade. Data on all clinic visits irrespective of reason for the visit will be extracted from ClinicLink. These will be used to describe patterns of health care use among the trial population. HIV-positive individuals receiving care in the clinics are not the recipients of the quality improvement interventions, which will be focussed on the nurses and systems for delivering care. Hence, interim visits for any intercurrent illness by patients will be managed as per standard clinical care and will not be routinely reported as adverse events.

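### The primary analysis leaves out baseline viral load status, although it is extracted for the whole main-analysis cohort; adjusting for it at patient level costs almost nothing and could add several points of power

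*Protocol article*

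**What the plan says.** Under Statistical analysis (Evaluation of the trial intervention), the primary outcome is analysed in two stages. Log clinic proportions are compared by a stratified t-test, and the effect is reported as an unadjusted ratio of geometric means. On precision, "The 95% confidence interval (CI) will be calculated with the variance estimated from the residual mean square" of an analysis of variance that includes stratum, arm and their interaction. The article then adds: "An adjusted analysis based on cluster-level summaries may also be done to account for covariate imbalance at baseline". That adjusted version uses a first-stage logistic regression without the arm term, followed by a comparison of log observed/predicted ratios. Its covariates are left to the analysis plan.

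Under Data collection (Evaluation of the intervention impact), VL results and dates are among the listed variables. The charts of the 150 evaluation-cohort participants per clinic "will be reviewed to extract these baseline data for entry into REDCap", and the review is repeated on the same people after 12 months.

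Under Allocation and blinding, clinics are stratified by size and "Restricted randomisation will be used to ensure balance between study arms on the following important covariates": the proportion male and the proportion under 25. Baseline VL status is not a balancing factor.

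**The concern.** With ten clinics, precision depends on how much clinics differ from one another. The baseline composite (VL documented and suppressed) is an earlier measurement of the outcome on the same patients. It is not balanced by design, and its ingredients are already being collected. The article does not leave the status of the two analyses open: it puts the unadjusted comparison first and makes adjustment discretionary, with imbalance rather than precision as its purpose. What is at stake is power that could be had without more clinics, patients or data.

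**Working it through.** **Inputs.** From Sample size justification: "With 5 clinics per arm, assuming a coefficient of variation, k, of 0.20, and a sample size of 150 patients per clinic"; control proportion p0 = 0.50 ("around 50% of patients in the control arm will have a VL measurement and be virally suppressed at the end of follow-up"); target "from 50% in the control arm to 77% in the intervention arm", so p1 = 0.77. Alpha is not stated for the power calculation; two-sided 0.05 is assumed, in line with the 95% interval.

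**The plan's own figure.** The usual formula for an unmatched cluster trial is

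c = 1 + (z_α/2 + z_β)² × [p0(1−p0)/m + p1(1−p1)/m + k²(p0² + p1²)] / (p1 − p0)².

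- Within-clinic part: 0.25/150 + 0.1771/150 = 0.00167 + 0.00118 = 0.00285.
- Between-clinic part: 0.04 × (0.25 + 0.5929) = 0.03372.
- Total: 0.03656. With (0.27)² = 0.0729 and (1.96 + 0.842)² = 7.849, c = 1 + 7.849 × 0.03656/0.0729 = 4.94.
- With c = 5, z_β = √(4 × 0.0729/0.03656) − 1.96 = 0.86, so power is 80.6%.

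The stated 80% is reproduced.

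**Where the variance lies.** 0.03372/0.03656 = 92% is between clinics. Table 1 shows the same thing: 100 and 150 patients per clinic both give 80% power for 50% versus 77%.

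**Power of the planned test.** Stratum, arm and interaction use 4 parameters, leaving 10 − 4 = 6 df. By noncentral t, power is 74.9% on the difference scale and 77.1% on the log scale. There is none to spare.

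**Upper bound on the gain.** If adjustment removed all the predictable clinic variation, k² would become k²(1 − r²). The formula then gives 80.6% at r = 0, 83.9% at 0.3, 89.6% at 0.5 and 96.8% at 0.7. No real adjustment achieves all of this.

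**Simulation of the article's residual method.** Assumptions: 3000 trials per scenario; strata of 4 and 6 clinics; individual baseline status by stratum in the first stage; log observed/predicted ratios tested with 6 df; patient-level latent correlation between baseline and follow-up of 0.3 or 0.5. The simulation standard error of one power figure is about √(0.75 × 0.25/3000) = 0.8 points. The last column instead adds the log clinic baseline proportion to the second stage, with 5 df.

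| r | Patient-level correlation | Unadjusted, 6 df | Individual baseline status, 6 df | Clinic-level covariate, 5 df |
|---|---|---|---|---|
| 0 | 0.3 | 74.1% | 73.8% | 63.3% |
| 0.3 | 0.3 | 73.8% | 75.5% | 67.7% |
| 0.5 | 0.3 | 74.7% | 78.8% | 73.3% |
| 0.5 | 0.5 | 72.8% | 79.6% | 73.1% |
| 0.7 | 0.3 | 74.5% | 80.5% | 82.9% |
| 0.7 | 0.5 | 74.2% | 85.0% | 84.5% |

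Type I error of the individual-level adjustment was 3.9% to 5.4%. A repeat simulation agreed: 75 versus 75% at r = 0, 75 versus 77% at 0.3, 73–74 versus 79–81% at 0.5, and 74 versus 81–84% at 0.7.

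For the clinic-level covariate, a run of 6000 trials per scenario gave 74% unadjusted versus 72% adjusted at r = 0.5, and 74% versus 77% at r = 0.6. Break-even is therefore near r = 0.55.

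**The case against.** An unadjusted comparison of cluster summaries is a legitimate primary analysis, and the article gives its reason: robustness with few clusters. The covariate list is properly left to an analysis plan that is not shown. Nothing in the documents fixes r. A documented VL after 12 months on ART was found for only 34% of the formative cohort, so a strong baseline-to-follow-up correlation cannot be taken for granted.

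Most of this stands, and it limits the point to an improvement rather than an error. It does not remove the point. The residual method is the article's own and is also based on cluster summaries, so the robustness argument covers it. The article itself ranks the unadjusted analysis first. Sparse VL values are not an obstacle to a yes/no composite, because a patient with no documented VL simply counts as no.

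Three stronger readings are tempting, and the text does not support them.

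- A reader might infer that adjustment happens only if imbalance is seen, so that the data choose the model. The article says that adjustment may be done to account for imbalance and that the covariates will be pre-specified.
- A reader might infer two competing main results. The unadjusted analysis is set out first and in full, and the adjusted one is additional.
- A reader might infer that sex and age under 25 are ignored. The restricted randomisation balances them, and whether they also enter the model is for the analysis plan.

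**Conclusion.** The point holds as a recommended improvement. The article fixes an unadjusted primary analysis and leaves adjustment optional, while a prior measurement of the outcome is collected on every member of the main-analysis cohort.

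For 50% versus 77%, individual-level adjustment moves power from about 74% by roughly 0 points at r = 0, +2 at r = 0.3, +4 to +7 at r = 0.5 and +6 to +11 at r = 0.7. These figures rest on an assumed r, assumed patient-level correlations of 0.3 to 0.5, strata of 4 and 6 clinics, and two-sided 5% testing.

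A reader might expect much larger gains from a clinic-level covariate: noncentral t with k² scaled by (1 − r²) and 5 df gives 82–84% at r = 0.5. That calculation ignores the variance added by chance imbalance of the covariate across ten clinics. With that included, power is about 73% at r = 0.5, which is no gain.

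**What to change.** State in the protocol and analysis plan that the two-stage observed/predicted residual analysis is primary. Its first-stage logistic model should contain stratum and each patient's baseline composite: VL documented and suppressed, yes or no, by the same definition of suppression as the primary outcome. Use only results dated before the intervention or its pilot began, with one calendar cut-off for both arms, so that the covariate cannot be affected by the intervention. Keep the planned second-stage test with 6 df, and report the unadjusted risk ratio as supportive. Do not add a clinic-level baseline covariate. Leave sex and age under 25 to the analysis plan.

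The cost is a wording change and slightly more analysis work; no new data are needed. One limitation should be acknowledged. Patients only just past 12 months on ART have a shorter pre-intervention window in which to have had a VL. If the 3-month pilot came immediately before recruitment (an assumption, since the timeline figure is not shown), a patient reaching 12 months as recruitment opened would have 12 − 3 = 9 months on ART before the cut-off. The composite is still defined for such patients, but it is somewhat less informative.

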### Trial oversight

It was not relevant to set up a data monitoring and safety board as routine health data will be assessed for study outcomes following the quality improvement intervention delivered to research nurses and augmentation of TIER.Net. Hence, we decided to set up a trial steering committee in addition to the trial management group.

#### Trial management group (TMG)

The trial management group will include the principal investigator and all the co-investigators including study statistician, research data manager, study coordinator and the operational managers of the five intervention clinics. The TMG will be chaired by the principal investigator and will have day to day oversight responsibility for the conduct of the trial.

They will meet once a month either in person or virtually to discuss the progress of the trial. They will also review all data from the trial and will be the main decision making body of the trial. They will be advised by an independent trial steering committee.

#### Trial steering committee (TSC)

This will consist of individuals who are independent from the study team. They will be joined by members of the TMG including the principal investigator, an investigator nominated by each collaborating institution, study statistician, study coordinator and research data manager. The composition will be specified in the TSC charter. The TSC will have operational responsibility for the overall conduct and management of the trial. The group’s terms of reference, roles and responsibilities will be defined in a standard operating procedure. One of the independent members of the TSC will act as the chair.

### Research ethics and consent

This study is registered with Clinicaltrials.gov (NCT05071573). The main study findings will be reported in accordance the Consolidated Standards of Reporting Trials (CONSORT) statement [20]. The study protocol v1.1, 19 Aug 2020 received ethical approval from the Biomedical Research Ethics Committee of the University of KwaZulu-Natal (BREC/1531/2020), the Research Governance and Ethics Committee of the Brighton and Sussex Medical School (ER/BSMS9B5G/4) and the KwaZulu-Natal Health Research Committee (KZ_202008_092). Any protocol amendments will need to be approved by all regulatory authorities mentioned above prior to implementation. Research staff will be trained in the amended protocol and any updated study materials and consent forms will be administered to the relevant participants as necessary. The University of Sussex is the sponsor of the study.

The operational managers of the 10 trial clinics will be given clear explanations about the trial aims, and the nature, scope, and possible consequences of their facilities and staff participating in the research by the study coordinator. Managers will be asked to provide written informed consent for their facilities to participate in the trial and be randomised to one of the two trial arms, and for review of clinical records of patients.

The principal investigator and study coordinator will schedule meetings with nursing staff from the 10 clinics, to explain the intervention and the trial aims. Nurses will be asked to consent to participation in the trial, and to receive further training as viral load champions if selected. They will be offered consent for participation in the process evaluation (not described in this protocol).

The informed consent process will be administered by a research assistant through REDCap with electronic signature obtained from nurses participating in the QIP. The nurses will be given paper copies of the participant information leaflets and consent forms.

A waiver of individual written consent from patients for a review of their clinical records is approved by all the regulatory authorities mentioned above. We requested this waiver for the following reasons: (1) the research involves minimal risks to the patients, (2) the extracted data will be anonymised hence there is no risk of the confidentiality of patients being compromised, and (3) analytical results will be reported at population or group level and not at the level of the individual patient.

We have a memorandum of agreement with the Department of Health to provide access to records in TIER.Net. Extraction of data from TIER.Net and ClinicLink, and linkage to other AHRI databases, has been previously approved by the University of KwaZulu-Natal Biomedical Research Ethics Committee (Ref: BE290/16).

### Data protection and patient confidentiality

All investigators and trial site staff will comply with the requirements of the Protection of Personal Information Act (or POPI Act) [21] which is the South African equivalent of the General Data Protection Regulation 2018 [22] with regards to the collection, storage, processing and disclosure of personal information and will uphold the Act’s core principles. Personal information will be collected, kept secure, and maintained. This will involve the creation of coded, depersonalised data where the participant’s identifying information is replaced by a unique identifier and the linking code is kept in separate locations using encrypted digital files within password protected folders and storage media.

### Dissemination

Research findings will be fed directly back to the community advisory board and the district and provincial departments of health prior to sharing this with the wider scientific community. In addition, under the existing memorandum of agreement between AHRI and the KwaZulu-Natal Department of Health, all scientific work (manuscript, conference abstracts) will be submitted for review by the department of health through the Head of the Health Research Committee. Study staff will feed results back to sites involved in collaboration with the department of health as they emerge and discuss areas that require strengthening. Investigators will publish findings in peer-reviewed journals and present at relevant conferences and meetings. Access to the final dataset will be according to AHRI data sharing policy available at https://data.ahri.org/index.php/home. Authorship of research manuscripts will follow the International Committee of Medical Journal Editors guidelines [23].

## Discussion

In the formative research leading up to the interventions proposed for evaluation in this protocol, we showed poor viral load monitoring and inadequate management of virological failure in HIV-positive patients on ART in rural KwaZulu-Natal, South Africa. Non-Nucleoside reverse transcriptase pre-treatment drug resistance exceeds 10% in the setting [24]; the threshold required to trigger a change in first-line ART using the public health approach [25]. In response to this, the South African ART guidelines now recommends dolutegravir, an integrase inhibitor in place of an efavirenz-based first-line ART [26]. Poor VLM may shorten the therapeutic lifespan of dolutegravir-based first-line ART due to development of resistance and predispose to poor clinical outcomes in HIV-positive individuals in public ART programmes in sub-Saharan Africa ([27]. Drug resistance is associated with increased morbidity and mortality with the risk of transmitting drug-resistant HIV to sexual partners.

The observed poor VLM in KwaZulu-Natal could be due to a number of reasons; patients may not have been aware of or empowered to request recommended blood tests, facility staff may be inadequately trained, or have insufficient time or resources to conduct blood tests when due, failure of results to reach clinics from the laboratory or failure to capture results on TIER.Net as these are manually entered [10]. The current study proposes to investigate the clinical and process impediments in VLM, including a review of patients’ clinical charts and comparing viral load in the charts with viral load data manually captured on TIER.Net in order to clarify whether the reported poor VLM was due to poor data entry in TIER.Net or actual failure to monitor viral loads. The proposed interventions will address all the steps potentially implicated in the poor management of VLM. This will involve training of staff on the current South African ART guidelines [26], designating a viral load champion who has administrative responsibility for identifying individuals due viral load tests or those with confirmed virological failure who need to be switched to second-line ART [17]. The automatic import of viral load results from the NHLS laboratories, also eliminates staffing challenges which contributes to backlogs in data capture and data entry errors. We also observed that amongst those with VLM who are experiencing virological failure, there is poor health system response to the clinical management of this situation. Only a minority of those with elevated viral load had a repeat viral load to confirm virological failure on ART, with only a small proportion of those with confirmed virological failure switching to second-line ART [10].

Hence there is urgent need to evaluate interventions that will improve VLM and the management of virological failure in ART programmes in sub-Saharan Africa. These interventions will have to be cost-effective, acceptable by patients and feasible to adopt in the health system. These additional important objectives will be addressed in this research but are not covered in this protocol. If the combination of interventions proposed for evaluation in this trial demonstrates effectiveness, the resulting early detection and prompt management of virological failure will be critical towards achieving UNAIDS 95-95-95 (95% of people living with HIV aware of their diagnosis, 95% of those diagnosed on ART and 95% of those on ART being virally suppressed) targets by 2030 [28].

